## Abstract

Dance can be an innovative, well-accepted, and effective therapy for stroke survivors. The present protocol aims to assess the feasibility of adapted Portuguese folk dance as a post stroke rehabilitative activity. We will use a mixed-methods pilot study convenience sampling to recruit 16 stroke survivors with mild–moderate lower limb paresis from a rehabilitation center in Lisbon and Tagus Valley. In addition to usual care, participants will attend 3 days per week 1-h dance exercise for 8 weeks. The dance style used for this intervention will be an adaptation of the Portuguese folk dance. Assessment will be conducted before and immediately after the program intervention. Acceptability will be assessed by four key domains (enrollment, retention, satisfaction, and recommendation to others). Safety will be assessed based on the number and type of adverse events. Feasibility will be assessed based on balance performance and functional mobility. Quantitative data will be analyzed through descriptive statistics for sample characterization, followed by inferential statistics to evaluate differences in the balance recovery and functional mobility scores between the initial and final assessment. Qualitative data will be analyzed using an inductive process of content analysis. The Portuguese folk dance program has the potential to improve balance outcomes and functional mobility. Our results will help validate Portuguese folk dance as a tool for rehabilitation settings for stroke survivors. The potential of our program to enhance balance outcomes and functional mobility among stroke survivors bears implications for aging and public health initiatives. Positive results from this study could pave the way for integrating dance-based rehabilitative activities into standard stroke rehabilitation protocols, catering to older stroke survivors’ specific needs and preferences.

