In Portugal, musical culture is part of the population’s roots. Portuguese folk dance is a group dance originating from the rural areas of Portugal. It is a movement art combining Portuguese folk songs with traditional folk dance. There are various kinds of dances stemming from different regions of Portugal. Nonetheless, although each dance employs a different technique, there are common traits in the various dances. All dances include circular movements and elaborate footwork, whether they consist of two or three steps, and dance in small circles or long lines (23, 24).

Considering the combination of complex and high-impact movements seen in Tango (15, 16) and Bolero (12) can improve the coordination and balance of patients with stroke, we hypothesize comparable outcomes with Portuguese folk dance.

Since folk dances are deeply rooted in the cultural heritage of a community, we expect that by incorporating a culturally specific intervention, stroke survivors can connect with their cultural identity, fostering a sense of belonging and familiarity. This can enhance motivation and engagement in the rehabilitation process. In addition, cultural activities have the potential to evoke positive emotions, such as joy, pride, and nostalgia (25, 26).

Therefore, engaging in familiar cultural practices, like folk dance, has the potential to reduce feelings of depression, anxiety, and social isolation (25). This positive emotional state can contribute to their overall well-being, motivation, and recovery.

This is the first know study that aims to find scientific evidence connecting Portuguese folk dance to balance and functional mobility improvement in stroke survivors. The implications of this study are manifold, particularly in the context of aging and public health. Aging populations increasingly face the challenges of stroke-related impairments, such as reduced balance and mobility, significantly impacting their quality of life. This study’s focus on stroke survivors addresses a crucial aspect of public health, as stroke incidence tends to rise with age, and effective rehabilitative interventions are essential for enhancing the well-being of this demographic. Therefore, our primary aim will be to assess the acceptability and feasibility of adapted Portuguese folk dance as a post-stroke rehabilitative activity.

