### Study design

2.1.

Program acceptability and feasibility will be evaluated with mixed methods using quantitative and qualitative assessments (27). To ensure quality in the research report, we followed the Good Reporting of A Mixed Methods Study (GRAMMS) checklist (28).

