### Data collection

2.5.

Participant characteristics: Participants’ sex, age, educational level, occupation, stroke history, comorbidities, MFAC and MoCA scores will be extracted from the participants’ clinical records.Researchers defined acceptability a priori by four key domains for developing the program and performing a subsequent randomized controlled trial. These key domains include enrollment (number of stroke survivors that participate in the program), retention (number of classes attended and percentage of enrolled participants who completed final program assessments), and satisfaction (assessed with a survey and semi-structured exit interviews).

Safety via adverse events (number of events involving injury).

The study coordinator, who will not be involved in performing the intervention, will administer a customized post-intervention survey to assess participants’ acceptability of the intervention. The questionnaire will consist of Likert scale questions to evaluate the participants’ satisfaction. The interviews aim to gain insight into participants’ perspectives on the intervention’s acceptability and usefulness and identify exercise preferences, barriers, and facilitators that may influence the stroke survivor’s participation in the program.

The following outcome measures will be collected in the week before (T0) and the week after completing the training program (T1) by the following instruments:

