Since this pilot study aims to determine the program’s acceptability and feasibility, our results will not allow us to determine that the participants’ health outcomes are due to the dance intervention. However, this study precedes the development of a randomized controlled trial that may prove the efficacy of adapted Portuguese folk dance as a therapeutic intervention for patients with stroke. If proven effective, the results should benefit stroke survivors by safely improving their balance and gait patterns. Additional benefits over clinical disease management, cognition, physical capacity, depression, and fear of falling are also expected. This will ultimately promote Portuguese folk dance as a rehabilitation intervention for stroke survivors, opening the door to testing its effectiveness, and acceptability in other populations in worldwide healthcare systems.

Although dance can be enjoyable, it can also be intimidating for people who have not previously participated in dance classes (47). However, incorporating Portuguese folk dance, part of the population’s cultural roots, in rehabilitation training can increase Portuguese stroke survivors’ adherence. In addition, this intervention has the potential to promote social interaction, as it will be performed in a group format. Therefore, we expect the participants to develop a sense of camaraderie (13, 14, 48) and accomplishment (14), contributing to the intervention’s satisfaction (13, 14). Given all these aspects, we believe incorporating Portuguese folk dance in rehabilitation training should be an especially well-adapted and attractive way of optimizing patient recovery after stroke.

As in previous studies that use dance intervention for stroke survivors in rehabilitation hospital settings, we expect the level of risks associated with the intervention to be low (14). However, the potential risks of a dance intervention should be anticipated and addressed to guarantee participants’ safety. Therefore, the instructor can adapt the exercise program and choreography to keep each participant’s skills and abilities challenging and engaging. In addition, as a safeguard, we will consider eight stroke survivors as the ideal number of participants for each session, depending on the stroke survivors’ dependence, thus achieving a ratio of two participants for one therapist.

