This study is not without limitations. First, the protocol will not include a control group, which will prevent comparing the effect of the dance intervention to additional treatment. Second, since stroke survivors are recruited in the subacute phase, some participants may suffer disease complications that stop them from attending the program.

Third, when assessing the program feasibility, we acknowledge the possibility of social desirability bias, as participants might report perceptions and feelings that might diverge from their emotions. Therefore, to minimize social desirability during the qualitative assessment, we will implement practices recommended by Bergen and Labonté (49). The interviews will be performed in a private location and not within earshot of others. The interviewer will use various approaches to establish rapport with participants, including humor, self-disclosure, and/or making displays of respect. We will clearly explain details about the study to participants, including how the data will be used and confidentiality and anonymity procedures. Suppose the interviewer suspects a response reflects social desirability tendencies. In that case, he will maintain a nonconfrontational and respectful posture and try to elicit a more accurate response by providing context when asking questions, acknowledging that people have diverse experiences, posing indirect questions, and requesting that participants provide a story or example to illustrate their response.

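### The Abstract defines feasibility, half of the primary aim, by uncontrolled before-after balance and mobility scores, which cannot show whether the program is workable and which conflict with other sections of the article

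*Protocol article*

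**What the plan says.** The Introduction sets the aim: "our primary aim will be to assess the acceptability and feasibility of adapted Portuguese folk dance as a post-stroke rehabilitative activity". The Abstract then gives acceptability, safety and feasibility a measure each. For feasibility it says "Feasibility will be assessed based on balance performance and functional mobility". For acceptability it says "Acceptability will be assessed by four key domains (enrollment, retention, satisfaction, and recommendation to others". Safety is the number and type of adverse events.

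Data collection and Quantitative evaluation put the balance and mobility part into practice: mini-BESTest and TUG in the week before and the week after the program, compared by a two-tailed paired t-test or a Wilcoxon signed-rank test. Neither section calls these scores feasibility measures.

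Other sections describe feasibility differently:

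- Study design: "Program acceptability and feasibility will be evaluated with mixed methods using quantitative and qualitative assessments (27".
- Discussion, limitations: "when assessing the program feasibility, we acknowledge the possibility of social desirability bias", which treats feasibility as resting on what participants report.
- Conclusion: feasibility and preliminary effects are named as two separate things to be assessed.

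On the health outcomes, the Discussion concedes that "our results will not allow us to determine that the" changes seen are caused by the dance.

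**The concern.** Feasibility asks whether a program can be run: whether patients join, attend, finish and come to no harm, and whether the sessions can be delivered. A change in a balance score among those who return for the final assessment answers none of this. It is an efficacy outcome, and here it has no comparator. Patients are recruited in the subacute phase and receive daily occupational and physical therapy alongside the dance, so scores may improve whether or not the program is workable.

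What is at stake is the wording of half of the primary conclusion. If the report follows the Abstract, its statement on feasibility will be drawn from mini-BESTest and TUG changes. The data that bear on feasibility will appear only under acceptability and safety. The Discussion presents this pilot as the step before a randomized trial, so a feasibility statement based on score changes would inform that step poorly.

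**Working it through.** **1. The statements side by side**

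| Section | What feasibility is tied to |
|---|---|
| Abstract | Balance performance and functional mobility |
| Introduction | Half of a joint aim with acceptability; no measure given |
| Study design | Mixed methods, quantitative and qualitative, jointly with acceptability |
| Data collection | No measure carries the name; mini-BESTest and TUG are called outcome measures |
| Discussion, limitations | Participants' reported perceptions |
| Conclusion | Separate from preliminary effects |

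Only the Abstract names a measure explicitly, and the other descriptions do not match it. A performance test is not subject to social desirability bias in the way the limitations paragraph describes. The Conclusion would be naming the same thing twice if feasibility were the change in balance and mobility.

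**2. Are process data planned?**

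Yes. Data collection lists enrolment, "retention (number of classes attended and percentage of enrolled participants who completed final program assessments", a satisfaction survey, exit interviews covering barriers and facilitators, and events involving injury. They are filed under acceptability and safety. Enrolment is a count of those who take part; no count of those invited is described, so an enrolment proportion has no stated denominator.

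**3. The plan's own numbers**

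- Sampling and recruitment: 16 recruited, allowing for 25% dropout. 16 × (1 − 0.25) = 12 completers, and 12 / 0.75 = 16, so the two figures agree. The 12 is back-calculated; the article does not state it.
- Intervention: 8 weeks × 3 sessions = 24 sessions per participant.

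**4. What process measures would give at this size**

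Exact (Clopper-Pearson) 95% limits for x of n are the 2.5% quantile of Beta(x, n − x + 1) and the 97.5% quantile of Beta(x + 1, n − x). With n = 16:

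| Completing final assessment | Proportion | 95% interval |
|---|---|---|
| 12 | 75% | 47.6% to 92.7% |
| 14 | 87.5% | 61.7% to 98.4% |
| 16 | 100% | 79.4% to 100% |

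If none of 16 participants were injured, the two-sided upper limit would be 1 − 0.025^(1/16) = 20.6%. These intervals are wide, but they describe the right quantity.

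**5. Illustration: the paired test as a yardstick**

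Assume two-sided alpha 0.05 (the article states none) and n = 12. Power is approximately P(T > 2.201), where T is noncentral t with 11 degrees of freedom and noncentrality d × √12.

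- d = 0.5: noncentrality 1.73, power 35%.
- d = 0.8: noncentrality 2.77, power 71%.

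A non-significant change would therefore say little about feasibility, and a significant one could reflect recovery or usual therapy.

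**6. Illustration: a retention cut-off of at least 12 of 16**

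P(X ≥ 12), with X binomial(16, p):

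| True retention | Chance of meeting the cut-off |
|---|---|
| 50% | 4% |
| 75% | 63% |
| 85% | 92% |
| 90% | 98% |

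Such a cut-off separates poor from good retention, but a program performing exactly at the plan's 75% would miss it 37% of the time (100% − 63%).

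**The case against.** The strongest reply is that the fault lies in one Abstract sentence. The body does not repeat it, the Conclusion already separates feasibility from preliminary effects, and the Discussion contrasts the acceptability and feasibility aim with attributing health outcomes. The data collected would be nearly the same after correction. This limits the size of the point but does not remove it. The Abstract sentence is the only explicit assignment of a measure to feasibility, and no other section supplies a replacement.

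Three stronger readings are tempting, and the article does not support them.

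- *The pilot cannot answer its own question, or gives no basis for the later trial.* Acceptability is the other half of the aim and is measured by process data. The article links those domains to the next step: "Researchers defined acceptability a priori by four key domains for developing the program and performing a subsequent randomized controlled trial".
- *A program that many abandon would be declared feasible if the rest improve, or a well-attended one infeasible if the test misses significance.* No section makes significance the feasibility rule, and retention would be reported in any case. The power figures are therefore illustrative only.
- *The lack of go/no-go cut-offs is itself an error.* What the article says was defined in advance is the domains, not thresholds. Numerical progression criteria may stand in a fuller document that is not shown.

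**Conclusion.** The point holds as a wrong and inconsistent definition. Feasibility, as the Abstract words it, rests on uncontrolled before-after efficacy scores that do not measure it and that the Discussion says cannot be credited to the dance. The acceptability half of the primary aim is unaffected.

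This judgment comes from comparing the sections; it does not depend on the power or cut-off calculations, which rest on an assumed alpha, assumed standardized changes and a back-calculated 12 completers. Correcting the definition changes what the pilot may conclude about feasibility, at almost no cost, so it should be done before enrolment starts.

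**What to change.** - **Abstract.** Replace the feasibility sentence. Assess feasibility by enrolment, sessions attended out of 24, the proportion of enrolled participants completing the final assessment, and adverse events.
- **Analysis.** Give exact 95% intervals for the proportions. Summarize attendance per participant.
- **Enrolment.** Also count the eligible patients invited, so that enrolment can be expressed as a proportion.
- **Mini-BESTest and TUG.** Relabel them as preliminary outcomes, used to estimate change and variability.
- **Consistency.** Align Study design, Data collection, the limitations paragraph and the Conclusion with the new definition. In the same pass, reconcile the acceptability domains: Data collection announces four but lists three, omitting recommendation to others.
- **Progression criteria.** Stating them before enrolment is advisable but secondary. Any cut-off needs its own justification. Bands such as 12 or more of 16 to proceed and 9 to 11 to amend are illustrations only, given the 63% pass rate at 75% true retention.

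The cost is wording changes and a simple screening log. No additional participants or assessments are needed.

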## Introduction

1.

Worldwide, stroke is the second leading cause of death and one of the leading causes of permanent disability (1, 2). As a result of the aging population and an increased survival rate, the absolute number of stroke survivors is rising (3). Many stroke survivors manifest some functional change (4). The most frequent impairments induced by stroke are centered on cognitive and motor disturbances, namely balance, coordination, proprioception, muscle tone, muscle strength, and gait (4, 5).

The 2016 American Stroke Association (ASA) and American Heart Association (AHA) guidelines recognize that stroke is a chronic condition and that many individuals require ongoing care to manage their needs. Therefore, they recommend expanding formal rehabilitation from the typical paradigm of 3–6 months (6). As a result of the rehabilitation process, many stroke survivors can regain functional capacity. Participation in rehabilitation programs that focus on balance and muscle-strengthening training is a factor that directly impacts the person’s recovery (7–9). However, limitations such as motor, visual, verbal, or informational memory loss, and impaired executive and social functions impact the patient’s ability to memorize the training steps and therefore hampers the effectiveness of rehabilitation programs (10).

In the last decade, numerous innovative rehabilitation interventions have emerged to address the needs of stroke survivors. Dance is increasingly used intervention to rehabilitate stroke survivors (11–15) Several investigations have shown that dance can be an effective treatment modality to address various impairments, with a relevant and sustained effect on psycho-emotional perspectives that can strongly enhance its use as rehabilitative activity (16–19).

Dance is a multidimensional intervention that exercises physical and motor skills and engages various cognitive functions such as perception, emotion, and memory (20). There is also evidence that dance can generate additional benefits in neurorehabilitation by inducing neuroplasticity (20).

For stroke survivors, dance can represent a therapy that enables enjoyable social activity and therapeutic exercise delivered at the appropriate intensity to improve balance, muscular strength, and mobility (12–15). In addition, dance can potentially improve stroke survivors’ self-esteem (21) and reduce the levels of psychological distress (22).

In Portugal, musical culture is part of the population’s roots. Portuguese folk dance is a group dance originating from the rural areas of Portugal. It is a movement art combining Portuguese folk songs with traditional folk dance. There are various kinds of dances stemming from different regions of Portugal. Nonetheless, although each dance employs a different technique, there are common traits in the various dances. All dances include circular movements and elaborate footwork, whether they consist of two or three steps, and dance in small circles or long lines (23, 24).

Considering the combination of complex and high-impact movements seen in Tango (15, 16) and Bolero (12) can improve the coordination and balance of patients with stroke, we hypothesize comparable outcomes with Portuguese folk dance.

Since folk dances are deeply rooted in the cultural heritage of a community, we expect that by incorporating a culturally specific intervention, stroke survivors can connect with their cultural identity, fostering a sense of belonging and familiarity. This can enhance motivation and engagement in the rehabilitation process. In addition, cultural activities have the potential to evoke positive emotions, such as joy, pride, and nostalgia (25, 26).

Therefore, engaging in familiar cultural practices, like folk dance, has the potential to reduce feelings of depression, anxiety, and social isolation (25). This positive emotional state can contribute to their overall well-being, motivation, and recovery.

This is the first know study that aims to find scientific evidence connecting Portuguese folk dance to balance and functional mobility improvement in stroke survivors. The implications of this study are manifold, particularly in the context of aging and public health. Aging populations increasingly face the challenges of stroke-related impairments, such as reduced balance and mobility, significantly impacting their quality of life. This study’s focus on stroke survivors addresses a crucial aspect of public health, as stroke incidence tends to rise with age, and effective rehabilitative interventions are essential for enhancing the well-being of this demographic. Therefore, our primary aim will be to assess the acceptability and feasibility of adapted Portuguese folk dance as a post-stroke rehabilitative activity.

